## Abstract

**Background:**

Social-emotional and behavioral problems are common in childhood. Early identification of these is important as it can lead to interventions which may improve the child's prognosis. In Dutch Preventive Child Healthcare (PCH), a new family-centered method has been implemented to identify these problems in early childhood. Its main features are consideration of the child's developmental context and empowerment of parents to enhance the developmental context.

**Methods/design:**

In a quasi-experimental study, embedded in routine PCH in the Netherlands, regions in which the family-centered method has been implemented (intervention condition) will be compared to "care as usual" regions (control condition). These regions are comparable in regard to socio-demographic characteristics. From more than 3,500 newborn babies, 18-month follow-up data on social-emotional and behavioral development will be obtained. PCH professionals will assess development during each routine well-child visit; participating parents will fill in standardized questionnaires.

Primary outcomes in the study are the proportion of social-emotional and behavioral problems identified by PCH professionals in children aged 2-14 and 18 months in both conditions, and the proportion of agreement between the assessment of PCH professionals and parents. In addition, the added value of the family-centered approach will be assessed by comparing PCH findings with standardized questionnaires. The secondary outcomes are the degree to which the needs of parents are met and the degree to which they are willing to disclose concerns.

**Discussion:**

The family-centered method seems promising for early identification of social-emotional and behavioral problems. The results of this study will contribute to evidence-based public health.

**Trial registration:**

NTR2681

## Background

Behavioral and social-emotional problems are common in childhood and may interfere severely with the everyday life of the child and his/her family [1,2]. Prevalence rates differ between studies and informants, with estimates ranging from 7% to 24% for children under 3 years of age [1,3-5]. For children aged 1 year, Briggs-Gowan et al. found that parents reported problems for approximately 6% of all children [1].

Early identification of social-emotional and behavioral problems, henceforth referred to as psychosocial problems, is important as it can lead to early intervention. Early intervention may help to optimize the environment of the child. This in turn may promote the development of the child [6-8], since the young brain is rapidly developing under the influence of both genes and experience [9-12].

Identification of psychosocial problems in young children is a difficult process, however. In infancy rapid developmental changes occur, along with behaviors which may seem deviant in older children but which can be part of normal development at younger ages [2]. Moreover, development of children is always embedded within a larger context, in which different factors such as, for example, characteristics of both parents and the child, constantly interact and influence each other, as reflected in the bio-ecological model of Bronfenbrenner [2,13]. Different factors may influence the development of children both in a positive or negative way, respectively labeled as protective factors; one example is adequate parenting, along with risk factors, such as lack of support. The influence of both risk and protective factors cannot be evaluated separately from each other; the balance between the burden experienced by parents, and the capacity and resources of the parents should always be evaluated.

The identification process is not only complex but also delicate. Ringing alarm bells too early can cause unnecessary stress, concern, and possible stigma for the parents. But when rung too late, parents may feel misunderstood, may lose trust in the care, their feelings of self-efficacy may decline, and problems may worsen [2]. To identify psychosocial problems or risk factors which may negatively influence psychosocial development, disclosure of any possible concerns by the parents is an important requisite [14-16]. Parental concerns have been described as being as accurate as quality screening instruments are [14]. Factors related to disclosure are: asking questions about psychosocial issues, expressions of support, and listening on the part of professionals [17].

Recently, a family-centered method, in which the above-mentioned difficulties, delicacies, and requisites are kept in mind, was introduced into Preventive Child Healthcare (PCH) in the Netherlands. PCH occupies a unique position in which to monitor psychosocial development closely, comparable to community pediatrics in the USA. Monitoring health and identification of psychosocial problems are mandatory tasks of PCH. PCH is free of charge regardless of insurance situation, and more than 90% of all children are seen regularly during routine well-child visits offered by Child Health Professionals, that is, nurses and doctors, henceforth referred to as CHPs.

As its name implies, the new approach is family-centered, which can be described as "placing the needs of the child, in the context of their family and community, at the centre of care and devising an individualized and dynamic model of care in collaboration with the child and family that will best meet these needs" [18]. The contents of the family-centered approach are based on the bio-ecological model of Bronfenbrenner [13] which reflects different child and contextual characteristics, and the interaction between these, influencing the development of the child. The model has been described as a promising framework for providing support to children in a successful way that is integrated into community-based services [19]. In the family-centered approach, the bio-ecological model is reflected in five different domains which are to be discussed with parents during each routine well-child visit and which concern the broad developmental context of the child. In addition to its contents, the family-centered approach is aimed at building a trusting and supportive relationship with parents in order to stimulate disclosure by and empowerment of the parents, and thus to enhance the positive psychosocial development of the child.

The family-centered approach seems to be a promising method for accurately monitoring psychosocial development, and the context in which infants grow up, in a way that enhances psychosocial development and early intervention if needed. In earlier research by Tan [20], internal validity and reliability of the family-centered approach were rated satisfactory. Furthermore, it was assessed that some domains of the family-centered approach showed a medium-significant correlation with the stress experienced by parents and family needs. The predictive value of the family-centered approach for identification of (risks for) social-emotional problems, along with the external validity of the five domains separately, were not studied by Tan, and is therefore still unknown.

The aim of this study is to assess the added value and the effectiveness of the family-centered approach in terms of how well it monitors psychosocial development and those factors which may influence psychosocial development, in infants of 0-18 months in a PCH setting. It is hypothesized that with the family-centered approach, CHPs will be able to identify psychosocial problems better, as compared to care as usual. Furthermore, it is hypothesized that, with the family-centered approach, the predictive values of the identification of psychosocial problems will be more accurate and that care will be better attuned to parents' needs and wishes and that parents will be more willing to disclose concerns, as compared to care as usual.

## Methods/design

### Design

In a quasi-experimental design, those regions in which the family-centered approach has already been implemented (intervention condition) will be compared to those regions where care as usual has been maintained (control condition). Overall, the regions in the family-centered care condition and the control condition are comparable for socio-demographic variables, including income, working participation, ethnicity, and percentage of single-parent households. In Figure 1 the design of the study is described schematically. Randomization per child/family is not possible in this setting as professionals provide care to all children in the region in which they work, in other words, contamination is inescapable in case of individual randomization. We will minimize the likelihood of contamination by prohibiting overlap between CHPs working in both the intervention and control conditions, and by informing CHPs about the activities to be undertaken for data collection in both conditions, separately. We chose a quasi-experimental design because full cluster-randomization was not possible due to implementation of the family-centered approach in a number of regions before the study started. To exclude those factors outside the intervention would affect the outcomes; no innovations regarding the psychosocial development of children aged 0-18 will be implemented in either the intervention or the control regions.

**Figure 1 F1:**
[figure not shown]
**Study design**. This figure describes the design of this study schematically.

The study has been approved by the Medical Ethics Committee of the University Medical Center Groningen. Participation is voluntary and all participants will be asked to give their informed signed consent. The CONSORT statement has been followed in describing the study [21].

### Participants

Consecutively, parents of all newborn babies, visiting a large Dutch PCH organization in a number of regions in the north of the Netherlands (parts of the provinces of Drenthe and of Overijssel), will be recruited for participation. Parents are eligible for participation if they visit a PCH center with their newborn before the child reaches 3 months of age and if they have sufficient mastery of the Dutch language to fill out the questionnaires used in the study.

### Training

Before the study began, we trained all CHPs for half a day. In the training we provided background information on the study and focused on the inclusion procedure, data collection, and enrolling "cases" in the study. Separate training sessions were held for CHPs from the control and intervention regions.

### Procedure

At the time of the routine PCH postnatal home visit, all trained CHPs will inform parents of children aged 2 weeks of their eligibility. The PCH nurse will provide an information package, including a letter, an information leaflet containing information about the study and its aims, and a small gift. CHPs will obtain informed consent from parents before the child reaches the age of 3 months and will subsequently send the consent form to the research institute. For parents who indicate that they do not want to participate, the CHP will ask whether the parent would agree to share some background characteristics (age, gender, country of birth, and employment status of the parents) and the assessment by the CHP of the psychosocial wellbeing of the child at 8 weeks of age. After the consent of the participants is received by the research institute, parents will receive a family-centered questionnaire by mail. At the end of the study, when a child is 18 months of age, parents will receive the family-centered questionnaire again and the Child Behavior Checklist (CBCL) 1.5-5 [22,23]. To enhance the filling out of the questionnaires by the parents, we will send reminders two weeks after sending out the questionnaires. Phone calls are planned one week after sending the reminder to those parents who have not yet returned the questionnaire.

During each routine well-child visit when the child is 2, 3, 4, 6, 9, 11, 14, and 18 months of age, CHPs will register in the medical records for all parents participating whether they have identified psychosocial problems or factors which might negatively influence psychosocial development. When an additional activity from the CHP is needed regarding psychosocial development (e.g., an additional appointment to assess the situation more in depth, an intervention, or a referral), that family (then referred to as a "case") will be asked by the CHP to take part in an interview consisting of several standardized questionnaires concerning the family-centered approach domains. If parents agree to participate, a trained interviewer will visit the parents at home to enhance the participation of risk groups. For each "case," two families will be invited for whom no additional activity was performed (control families). Children will be matched by age, gender, and region (intervention or control). All the families who are interviewed together will form the subsample in our study.

To enhance the compliance of all CHPs, we will monitor all the results (such as inclusion percentages and filling in medical records) very closely from the start and will present these during team meetings. To minimize missing data from CHPs, data collection in the medical records will be closely monitored. When CHPs fail to fill in information for a participating child, they will receive an e-mail with the request to fill in the information in retrospect if possible. To minimize parental attrition, all participating children will be sent a birthday card for their first birthday. At the end of the study, when the child is 18 months of age, all participants will receive a small gift.

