The family-centered approach covers five domains associated with psychosocial development which are discussed from the perspective of parents. Domains discussed are: Competence of the parent, Role of the partner, Social support, Perceived barriers or life events within the care-giving context, and Wellbeing of the child. For each domain, several questions regarding that specific domain are asked, intertwined in a conversation, by the CHP (see Additional File 1: Appendix 1). During the second well-child visit at age 8 weeks, the nurse is allotted 15 minutes extra (added to the routine 15 minutes, i.e., 30 minutes in total) to discuss the 5 domains exhaustively. During every routine well-child visit, any possible parental concerns will first be elicited which will provide a starting point for further communication. For all the questions in the family-centered approach, CHPs will be able to register important information as not discussed, a protective factor, not known, or a risk factor. Furthermore, for each domain, the results of the conversation will be able to be summarized as not discussed, a protective factor, not known, or a risk factor, and subsequently an explanation will be able to be provided. Based on the information about the different domains, the parent and the CHP will jointly decide whether there are any concerns. If there are any, an additional activity (for example, an appointment to further clarify these or an intervention) will be planned. In communication with the parents, building a relationship of trust and empowerment of the parents are central features of the family-centered approach. Parents are regarded as experts on their child and in their own strengths, which may function as protective factors that can be enhanced to stimulate positive psychosocial development of the child.

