### Sample size and power calculation

In a study regarding children aged 2-4 years, PCH identified psychosocial problems in 10-12% of all children, of these 22-23% were confirmed by clinical scores on the CBCL filled in by parents [37]. For the current study, an increase in the predictive value of 20% for the family-centered approach is considered to be relevant, resulting in an identification rate of 42%. With a power of 80% and a .05 alpha, 85 "cases" in both regions of the country will be needed to detect a change in predictive value of 20%.

Based on birth statistics in both the intervention and control regions, approximately 2,500 births are expected [38] within one year in both the intervention and control regions. With an expected participation rate of 70%, this would result in 1,750 participating families in both conditions within the inclusion period of one year. With an expected cumulative incidence of 10% of children with social-emotional problems between 2 and 14 months, this would result in 175 "cases" in both conditions. We anticipate that 70% of "cases" will agree to participate, so that 121 "cases" and 242 matching control families can be invited for complementary interviews. For this group, we anticipate that for 70% of included "cases" a complete dataset will be collected.

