### Statistical analyses

To compare the baseline characteristics of the participants in the intervention and control regions, chi-squared tests for categorical variables and t-tests for continuous variables will be used. If the intervention and control regions differ regarding the background characteristics of the children, appropriate multivariable analyses will be done using standard and logistic regression analyses to adjust for these differences.

Regarding the primary outcomes of the study, the following analysis will be performed. First, we will compare the proportion of, and risks for psychosocial problems identified by the CHPs in both the intervention and control conditions when the child is between 2 and 14 months of age and when the child is 18 months of age, using chi-squared tests and logistic regression analysis to correct for potential differences between regions. Second, we will assess the sensitivity, specificity, and the positive and negative predictive values of social-emotional and psychosocial problems identified by CHPs in both conditions, using the ASQ-SE [25,26] for children aged 2-14 months from the subsample and using the CBCL [22,23] for all participating children when the child is 18 months of age. Third, we will compare kappas as a measurement of agreement between the protective and risk factors assessed by the CHPs, and relevant reference questionnaires as filled in by the parents from the subgroup.

For the secondary outcomes of the study, we will compare met and unmet needs of the parents between conditions using independent t-tests and multivariate regression analysis to correct for potential differences in background characteristics. The level of willingness to disclose concerns will be compared using ordinal regression analysis.

Data will be analyzed using SPSS 18.0. The significance level is set at .05.

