### Strengths

We expect the findings of this large prospective quasi-experimental study into the daily practice of PCH to be very useful for practitioners and policymakers. Inclusion and exclusion criteria are set so as to highly resemble routine care in order to obtain generalizable findings. For the same reason, we will be investing a great deal in order to enhance the participation of all parents. For example, before the study started, we were able to focus media attention on the study in order to interest potential participants. Furthermore, in the information packet for parents, a small gift is provided to further spark the interest of the parents, and when we wrote the information flyer we made use of input from the CHPs so as to appeal to parents. For that part of the subsample in which an additional activity is to be carried out by a CHP, the parents will be informed by their own CHP and thereafter will be contacted by an interviewer who will visit the families at home. Interviewers are all well trained and have very good communication skills which should enhance participation of families. To further facilitate the participation of parents, we trained all the CHPs before the study started, interactively informing them how to motivate parents adequately and, if necessary, to remove any barriers felt by parents.

Besides evidence regarding the effectiveness of identifying the risks for psychosocial development, our study will also provide insight into whether parents experience the family-centered approach as truly family-centered. This insight may be very useful for the design of further training sessions for the CHPs. Furthermore, the evidence about whether parents feel free to disclose possible concerns to their CHP may provide interesting and important information. Disclosure by parents seems a sine qua non for the early identification of, and risks for, psychosocial problems. Parental concerns have even been shown to be as accurate as other screening methods such as questionnaires [14].

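### The 2-14 month predictive value rests on flagged families who agree a second time and complete the interview, and this selection, which could differ by condition, is neither measured nor corrected

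*Protocol article*

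**What the plan says.** Parents consent to the main study before the child is 3 months old (Protocol article, Procedure). If a CHP later decides that an additional activity is needed, the family becomes a case and "will be asked by the CHP to take part in an interview consisting of several standardized questionnaires". The Strengths section makes clear who asks: "the parents will be informed by their own CHP and thereafter will be contacted by an interviewer". A second agreement is therefore required: "If parents agree to participate, a trained interviewer will visit the parents at home to enhance the participation of risk groups". The analysis group follows from it: "All the families who are interviewed together will form the subsample in our study".

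Statistical analyses then computes sensitivity, specificity and predictive values at 2-14 months "using the ASQ-SE [25,26] for children aged 2-14 months from the subsample". At 18 months the reference is the CBCL, planned for all participating children.

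On expected yield, the sample size section says "We anticipate that 70% of 'cases' will agree to participate", and that 70% of the included cases will give a complete dataset.

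On how a concern is reached, the intervention section says that "the parent and the CHP will jointly decide whether there are any concerns". The section on care as usual describes no corresponding step.

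Potential limitations names selection bias and lists measures to encourage participation, including in the subsample. The comparison data it describes come from parents who decline the main study.

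**The concern.** PPV is a proportion among flagged children. If flagged children who would score positive on the ASQ-SE are more, or less, likely to reach a completed interview than those who would score negative, the PPV among completers differs from the PPV among all flagged children. Two features make this plausible here. The reference standard is the parent's own report, so the parent's perception may govern both acceptance and score. And the route to being flagged differs: intervention parents have taken part in deciding that there is a concern, while the article describes nothing of the kind for control parents. Willingness to disclose is itself expected to differ between conditions (Background, hypotheses).

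The sample size rests on a rise in predictive value of 20 points, so a selection effect that differs by condition acts directly on the contrast of interest. It is separate from the two-controls-per-case matching, because PPV is computed within cases, and from refusal of the main study.

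**Working it through.** **Inputs from Sample size and power calculation.** 2,500 births and 70% participation per condition; 10% cumulative incidence; 70% of cases agree; 70% of included cases complete; predictive value 22% against 42%; power 80%; alpha 0.05; 85 cases per condition.

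**The plan's own figure.** Two-sided comparison of two proportions, pooled variance, no continuity correction, with mean proportion 0.32:

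n = [1.960 × √(2 × 0.32 × 0.68) + 0.842 × √(0.22 × 0.78 + 0.42 × 0.58)]² / 0.20² = 84.2, so 85 per condition. This reproduces the stated number.

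**Case flow per condition.**
- 2,500 × 0.70 = 1,750, as the plan says: "this would result in 1,750 participating families in both conditions within the inclusion period of one year".
- 1,750 × 0.10 = 175 cases.
- 175 × 0.70 = 122.5 (the plan states 121).
- 121 × 0.70 = 84.7, about 85.

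The required 85 is thus met by cases who both agree and complete. As a share of all flagged cases this is 0.70 × 0.70 = 49%. The second 70% refers to a complete dataset across many instruments, so a family with an incomplete dataset may still have an ASQ-SE. The contributing share therefore lies between about 49% and 70%.

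**Illustration of selection.** Let p be the true PPV, s the overall completion share, a and b the completion probabilities for cases who would score positive and negative, and OR their odds ratio. Solve

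p·a + (1 − p)·b = s, with [a/(1 − a)] / [b/(1 − b)] = OR.

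The observed PPV is then p·a/s. With p = 0.22:

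| OR (assumed) | s = 0.49: a, b | Observed PPV | s = 0.70: a, b | Observed PPV |
|---|---|---|---|---|
| 1 | 0.490, 0.490 | 22.0% | 0.700, 0.700 | 22.0% |
| 1.5 | 0.569, 0.468 | 25.5% | 0.763, 0.682 | 24.0% |
| 2 | 0.623, 0.452 | 28.0% | 0.803, 0.671 | 25.2% |
| 3 | 0.695, 0.432 | 31.2% | 0.852, 0.657 | 26.8% |

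**Consequence for the contrast.**
- Selection of this kind in the control condition only, with an intervention value of 42%: the 20-point gap appears as 42 − 25.5 = 16.5 down to 42 − 31.2 = 10.8 points at 49% completion, and as 42 − 24.0 = 18.0 down to 42 − 26.8 = 15.2 points at 70%. A true effect is partly masked.
- The same selection in the intervention condition only, with 22% true in both: an apparent gap of 3.5 to 9.2 points at 49%, or 2.0 to 4.8 points at 70%, arises without any true difference.

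**What exists for cases not interviewed.** CHP ratings at each routine visit, baseline characteristics, the family-centered questionnaire at 2 months with the disclosure item, and the 18-month CBCL are planned for all participating families (Procedure; Measurements). The ASQ-SE is not.

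**The case against.** A reader might infer that this selection favours the intervention and manufactures part of the target difference. The documents do not support that. The mechanism they most readily suggest, control parents who see no problem declining more often, raises the control PPV and shrinks the observed gap. Even that rests on the article's silence about how concerns are shared in usual care, which is summarised by reference to national guidelines not shown here. The same case definition, an additional activity being needed, applies in both conditions.

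It can also be said that the illustration is soft. That stands: the odds ratios are assumed, the upper shifts need completion as low as 49%, and the 22% is a CBCL confirmation rate in children aged 2-4 years, not an ASQ-SE value in infants.

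The plan does invest in participation, with home visits, trained interviewers and CHP instruction. These may reduce refusal but do not show who was lost.

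Weighting on early covariates would not capture what the parent thought when the child was flagged, so it removes only the measured part of the selection. That also stands.

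The 18-month predictive value based on the CBCL does not pass through the interview, and the Outcome measurements section can be read as already wanting 2-14 month identification assessed against 18 months. Statistical analyses does not state that cross-tabulation, however. Finally, weighting and responder comparisons are often left to a fuller plan. But the article does state both the analysis group and its selection-bias comparison, and that comparison stops at refusal of the main study.

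**Conclusion.** The point holds as a modest, inexpensive improvement. As written, the 2-14 month predictive value is an estimate among interviewed families, expected to be about 49% to 70% of flagged cases, and nothing described measures or corrects selection at this second step. Selection could create or mask part of the 20-point difference. Under the assumptions above (true PPV 22%, completion odds ratios 1.5 to 3, selection in one condition only), the shift is about 3.5 to 9 points at 49% completion and 2 to 5 points at 70%. Neither its actual size nor its direction can be derived from the documents. The CBCL-based value at 18 months is not affected by interview refusal.

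**What to change.** In Statistical analyses:

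(a) State that, for each condition, identification at 2-14 months will also be evaluated against the 18-month CBCL in all participating cases with a CBCL, whether or not they were interviewed, as a supporting analysis.

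(b) Compare interviewed and non-interviewed cases, by condition, on baseline characteristics, the early family-centered questionnaire including the disclosure item, and CHP ratings. Add an inverse-probability-weighted ASQ-SE analysis, with completion modelled within condition, as a sensitivity analysis, and say that it corrects only for measured predictors.

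**Cost.** Some wording and programming; no new data or contacts. Intervals widen slightly after weighting. The CBCL comes later and may follow the additional activity, so (a) supports the ASQ-SE analysis and does not replace it.
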